Skånes Universitetssjukhus - Lund

[name]

Sweden

Expected initiation date 2014

Expected termination date 2020.

The study will be conducted according to the study protocol, the national legislations, and the ICH-GCP guideline.

The National Medicinal Authorities, the National Ethical Committees and the National Data Protection Agencies will be notified of the study.

The Study has been registered at clinicaltrials.gov

**1.2 Abbreviations.**

AE Adverse Event

bALP Bone specific Alkaline Phosphatase

BON Bisphosphonate Induced Osteonecrosis of the Jaw

Clcr Creatinine Clearance

CRF Case Report Form

CT Computed tomography

CTX-I C-terminal cross-linked Telopeptide of type I Collagen

ICTP C-terminal cross-linked Telopeptide of type I Collagen generated by MMPs

MGUS Monoclonal Gammopathy of Undetermined Significance

MM Multiple Myeloma

PINP Procollagen type I N-terminal propeptide

PBD Progressive Bone Disease

sPBD Symptomatic Progressive Bone Disease

SAE Severe Adverse Event

SAR Serious Adverse Reaction (expected)

SRE Skeletal Related Event

SUSAR Suspected Unexpected Serious Adverse Reactions

TRAP5b Tartrate Resistant Acid Phosphatase isotype 5b

QoL Quality of Life

**1.3 Background.**

Treatment with bisphosphonate.

Multiple myeloma (MM) is a B-cell malignancy characterized by proliferation of monoclonal plasma cells in the bone marrow. One of the most devastating complications in MM is the severe loss of bone mass observed in the majority of the patients. Bone loss can either be observed as typical osteolytic lesions or as a more generalized osteopenia. At diagnosis, 79 percent of all patients present with abnormal findings on conventional radiography either caused by osteolytic lesions, fractures, or osteoporosis; furthermore, bone pain is present in 58 percent of the patients [[1](#_ENREF_1)]. Up to 90 percent of all patients will eventually suffer from bone destruction, which may result in pain, pathological fractures, nerve root compression, or hypercalcaemia [[2](#_ENREF_2)]. Because of this, patients with MM have a severely reduced quality of life (QoL) [[3](#_ENREF_3)]. Since Berenson *et al*. in 1996 demonstrated that the use of the bisphosphonate pamidronate can reduce the number of skeletal related events (SRE) and diminish pain, bisphosphonate has been the cornerstone in treating bone disease in MM [[4](#_ENREF_4)]. In 2003, the more potent bisphosphonate zoledronic acid was demonstrated to be “non-inferior” to pamidronate in reducing SRE in MM [[5](#_ENREF_5)]. Later it was demonstrated that zoledronic acid not only reduced the number of SRE but also increased overall survival with 5.5 months [[6](#_ENREF_6)], an association that had been very difficult to demonstrate for pamidronate [[7](#_ENREF_7)]. Likewise it has been demonstrated that patients without bone disease at diagnosis; evaluated with conventional radiography; may benefit from zoledronic acid. A significant reduction in the incidence of SRE has been observed in this subgroup of patients when zoledronic acid is initiated already at diagnosis [[8](#_ENREF_8)].

Duration of bisphosphonate treatment.

In 2003 it was first suggested that treatment with bisphosphonates could cause bisphosphonate induced osteonecrosis of the jaw (BON) [[9](#_ENREF_9)]. BON is a serious disorder where the bone, usually of the mandible, starts to dissolve. The incidence in BON increases with the duration of bisphosphonate treatment and the potency of the bisphosphonate; and is commonly observed subsequently to tooth extraction [[10](#_ENREF_10), [11](#_ENREF_11)]. Because of BON, various recommendations regarding preventive initiatives have been published on how to reduce the incidence of this side effect. These preventive initiatives include; high-risk dental conditions should be treated prior to bisphosphonate initiation, good oral hygiene should be maintained throughout the treatment period, after treatment initiation invasive dental procedures should be avoided if possible, prophylactic antibiotics should be given in case of invasive dental procedures, and the duration of bisphosphonate treatment should if possible be limited [[2](#_ENREF_2), [12](#_ENREF_12)]. In combination, these preventive initiatives have reduced the incidence of BON [[13](#_ENREF_13), [14](#_ENREF_14)]. Concerning the duration of bisphosphonate treatment, most guidelines suggests two years of treatment after which further treatment should be at the discretion of the treating physician [[2](#_ENREF_2), [15](#_ENREF_15)]. The reason for the two years separation is based on very little scientific evidence. But, the two initial bisphosphonate studied had a follow-up of 21 and 24 months respectively [[5](#_ENREF_5), [7](#_ENREF_7)]. There are scarce data concerning what happens once bisphosphonate is discontinued in MM. However we do know that biochemical markers of bone resorption start to increase shortly after discontinuation, and that the rate of the increase is greater if the preceding treatment duration is short [[16](#_ENREF_16)]. Likewise there are data indicating that early re-initiation of bisphosphonate may prevent development of progressive bone disease (PBD) [[17](#_ENREF_17)]. These data could suggest that, by withholding bisphosphonate in order to avoid BON, the patient is subjected to an increased risk of bone pain, hypercalcaemia, or fractures. This schism is becoming increasingly relevant as the expected life time of the patients is increasing these years, thus resulting in a prolonged time period where the patient perhaps receives inferior treatment due to fear of potential side effects.

Bone markers in multiple myeloma.

Throughout life, bone is continuously being remodelled with removal of old bone by the osteoclast followed by replacement with new bone by the osteoblast. In MM, bone resorption is generally increased both in regard to numbers and activity of the osteoclast. Bone formation on the other hand follows a more biphasic pattern, being compensatory increased early in the disease, but later as the disease progresses it becomes depressed [[18](#_ENREF_18), [19](#_ENREF_19)]. This imbalance ultimately leads to loss of bone mass and osteolysis. Biochemical markers of bone remodelling are components that are released to the blood during the bone remodelling process. Unlike bone imaging, which provides static data, bone markers provide dynamic information on the current bone turn over rate [[20](#_ENREF_20)]. Furthermore, bone markers can be measured in a blood sample, hopefully negating the need for radiation. Bone markers can be divided into markers of bone resorption and markers of bone formation, thus evaluating each part individually. Recently we have demonstrated that changes in the levels of different bone markers preceded progressive bone disease (PBD) in the individual patient [[21](#_ENREF_21)]. We therefore hypothesis that, in the future, development in bone marker levels in the individual patient can be used to tailor bisphosphonate treatment in the individual patients, as opposed to treatment for a fixed time period in all patients. Our hope is that treatment could be initiated as soon as bone turnover becomes abnormal instead of waiting for painful osteolysis to develop. Likewise, treatment could be withheld when bone remodelling becomes stable thereby avoiding unnecessary side effects. In this study, we want to collect markers of bone resorption and bone formation and thus retrospectively be able to calculate cut of values for the different markers where the best positive- and negative predictive values are achieved. Since this parameter is partly explorative it will the needed afterwards to design prospective trials where we test the clinical usefulness of bone marker guided treatment. Another way to separate the markers is into extracellular components released during the actual bone remodelling process or into cellular components reflecting the number of osteoclasts or osteoblasts respectively. The extracellular markers profit from being highly specific but are also subject to high variation, whereas the cellular markers are less specific but more stable. We also want to use this study to investigate if it is the more specific markers of actual bone remodelling or the more stable cellular markers that are the safest to use in a future prospective clinical trial. The following bone markers will be measured: C-terminal cross-linked Telopeptide of type I Collagen (CTX-I), a bone degradation marker reflecting actual collagen breakdown. Tartrate Resistant Acid Phosphatase isotype 5b (TRAP5b), a bone degradation marker reflecting the number of osteoclasts. Procollagen type I N-terminal propeptide (PINP), a bone formation marker reflecting collagen synthesis. Bone specific Alkaline Phosphatase (bALP) a bone formation marker reflecting the number of osteoblasts, and C-terminal cross-linked Telopeptide of type I Collagen generated by MMPs (ICTP), a bone degradation marker reflecting matrixmetalloproteinase-induced collagen breakdown. ICTP will be measured only at diagnosis. For further details on when bone markers will be measured, please see section 1.7 and appendix 1.

Bone imaging in multiple myeloma.

Despite recent advances in imaging techniques, conventional radiography remains the golden standard when evaluating bone disease in MM [[22](#_ENREF_22), [23](#_ENREF_23)]. Presence or absence of osteolytic lesions may define if a patient is ultimately diagnosed with asymptomatic MM (which results in a watch and wait strategy) or active MM (which results in chemotherapeutic treatment). The rational behind this is that patients with osteolytic bone disease rapidly progress to more active disease if left untreated [[24](#_ENREF_24)]. Conventional radiography however, is known to have a low sensitivity since at least 30% of the trabecular bone substance must be lost before osteolytic lesions becomes detectable; likewise areas such as the scapula, the ribs, and the sternum can be difficult to visualise [[22](#_ENREF_22)]. Computed tomography (CT) scanning is superior to conventional radiography in detecting osteolytic lesions, however due to the high radiation exposure it seems inappropriate to use this modality as a screening tool [[25](#_ENREF_25)]. However, because of the advances in radiology it is now possible to design whole body low-dose CT protocols, reducing the radiation exposure from 25.5 mSv to 4.1 mSv (conventional radiography 2.4 mSv) without loosing the visualisation capabilities of the CT [[26](#_ENREF_26)]. Furthermore, low-dose CT is much quicker to perform and less cumbersome for the patients compared to conventional radiography of almost the entire skeleton. Few studies exists which systematically evaluate the use of low dose CT in MM. One prospective study included 39 persons diagnosed with either MM or Monoclonal Gammopathy of Undetermined Significance (MGUS) allowing both initial and restaging scannings to be included [[27](#_ENREF_27)]. A more recent study evaluated retrospectively acquired data from low-dose CT and PET-CT in 51 persons also including both initial and restaging scannings [[28](#_ENREF_28)]. Both studies found low-dose CT to be superior to conventional radiography in detecting bone disease. However, the clinical relevance of these findings remains to be determined.

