To investigate if monthly measurements of the bone markers CTX-I, PINP, bALP, TRAP5b, or the ratios of these can be used to predict the development of PBD from year 2 to year 4.

To investigate the consistency between the finding “no bone disease” when using conventional radiography compared to low-dose CT at diagnosis*.

To investigate if the patients with inconsistency in bone disease status using the different imaging modalities at diagnosis are more likely to progress in bone disease compared to patients diagnosed with “no bone disease” using both modalities*.

To investigate if the three patients groups 1. consistent “no bone disease” 2. inconsistent bone disease 3. consistent “bone disease”, at diagnosis can be identified using the levels of the bone markers CTX-I, PINP, bALP, TRAP5b, ICTP, or the ratio of these.

* Sites may participate in the study without conduction both conventional radiography and low-dose CT.

Amendment: The primary endpoint will not be affected by the amendment. The eight first secondary endpoints will not be affected by the amendment. The last three secondary endpoints will be affected by the amendment, but it is without statistical relevance; see section 1.13

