**1.13 Statistical Considerations.**

Primary endpoint:

There are no published data on the incidence on PBD from year 2 and onward in MM. However, there are data showing the annual incidence of the more strict sPBD is approximately 5% in patients receiving continuous zoledronic acid [[31](#_ENREF_31)]. Since we in this study use a less strict definition of progression in bone disease, we assume the annual incidence will be 7.5% instead of only 5% in patients receiving zoledronic acid. Based on data from the MRC IX trial and from an ASH publication in 2012 we expect to see risk reduction rate of 0.5 [[32](#_ENREF_32)]. With a significance threshold of 0.05, one-sided, a power of 80, and a fixed study duration of 2 years, we need a sample size of 143 per group to detect a difference in the primary endpoint. 286 patients in total need to be allocated to the two treatment arms. However, due to the nature of the disease, 30% of all patients will be dead before year two. Due to the in- and exclusion criteria we presume that only 20% of the study population will be dead before stratification. Thus 358 patients in total need to be included in the protocol. Data will be analysed according to the treatment the patients actually received using the Kaplan-Meier analysis. Patients will be analysed per protocol. New data have shown significant reduction in PBD after 4 years treatment with zoledronic acid compared to 2 years of treatment in 170 randomised patients^33^.

Other endpoints:

Serum samples will be collected and stored from all patients. From the calculations above, we expect 32 cases of PBD during year two to four. Bone markers will be measured on these patients from the time of PBD and 6 month prior to the bone event. An equal number of controls will be selected as the number of cases PBD actually observed and bone markers will be measured likewise in these patients. The controls will be selected according the stratification criteria’s (previous autologous stem cell treatment, presence or absence of bone disease at diagnosis, and previous treatment with bortezomib). If multiple options are present the same gender will be chosen, and after that the closest age related. Data will be analyzed as a case control study

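### Bone-marker cut-offs are to be chosen for the best PPV and NPV in about 32 cases and 32 controls, so predictive values read from those same patients will be too high

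*Protocol*

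**What the plan says.** All references are to the Protocol.

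- **1.3 Background (bone markers)** gives the selection rule. The trial should "retrospectively be able to calculate cut of values for the different markers where the best positive- and negative predictive values are achieved". Directly afterwards the section limits this claim and leaves the test of marker-guided therapy to later trials: "Since this parameter is partly explorative it will the needed afterwards to design prospective trials where we test the clinical usefulness of bone marker guided". The same section wants the data to show which class of marker, the specific extracellular or the more stable cellular, is safer to take into a later prospective trial.
- **1.4 Study Rational** makes marker-tailored treatment one of three purposes of the study.
- **1.5 Study Objectives** lists a secondary endpoint whose outcome is PBD in the two years after randomisation: "To investigate if monthly measurements of the bone markers CTX-I, PINP, bALP, TRAP5b, or the ratios of these can be used to predict". That is four markers and up to six pairwise ratios.
- **1.13 Statistical Considerations** fixes the data. It counts on 32 PBD cases after randomisation and has their markers assayed over the half year leading up to the event. For the comparison group, "An equal number of controls will be selected as the number of cases PBD actually observed". The method is given in one line: "Data will be analyzed as a case control study".
- **1.15 Privacy of Personal Data and Data Handling** confirms that monthly markers are assayed only in the 32 cases and 32 controls. The bi-annual samples are assayed in all patients.

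The protocol gives no test, significance level or pass mark for the markers.

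**The concern.** Choosing the cut-off that performs best, and then quoting its performance in the same patients, credits the marker with whatever chance contributed to its being chosen. With 64 patients and several markers that contribution is large. The rule also always returns a best cut-off, whether or not any marker carries information.

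The result is meant to be used. It is to inform which markers, and at which cut-offs, a later trial of marker-guided bisphosphonate treatment would test. Inflated values could put a noise-selected cut-off into that trial, or make its designers expect more than the marker can deliver. The bias does not depend on how the controls are matched and would remain with ideal controls.

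**Working it through.** **1. The plan's own figure.** Section 1.13 assumes a yearly PBD incidence of 7.5% on zoledronic acid and a risk ratio of 0.5, hence 15% off treatment, with 143 patients per group.

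- One year of these rates: 143 × (0.075 + 0.15) = 32.2, which reproduces the 32 cases.
- Two years, exponential: 143 × [(1 − e^−0.15) + (1 − e^−0.30)] = 143 × (0.139 + 0.259) = 57.
- Two years, compounded: 143 × [(1 − 0.925²) + (1 − 0.85²)] = 60.
- Two years, linear: 143 × (0.15 + 0.30) = 64.

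I therefore checked 32 v 32 as planned, and 60 v 60 in case two years of events are seen.

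**2. What is selected.** For the k patients on the high side of a cut-off, of whom a are cases:

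- PPV = a/k
- NPV = (32 − (k − a))/(64 − k)

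Without a marker effect both have expectation 0.50 at any fixed cut-off. Example: k = 20 and a = 14 gives PPV = 14/20 = 0.70, NPV = (32 − 6)/44 = 0.59 and a mean of 0.645. At one fixed cut-off, a has mean 10 and SD √(20 × 0.5 × 0.5 × 44/63) = 1.87, so 14 lies about 2.1 SD above expectation. A search over cut-offs reaches this level on average.

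**3. Simulation with no marker effect.** Assumptions, none stated in the protocol:

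- four normal log-markers with pairwise correlation 0.3 or 0.6
- ratios taken as differences of logs
- one time point
- either direction allowed
- at least 6 or 13 patients on each side of the cut-off

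In each simulated trial the cut-off maximising PPV + NPV was kept. The table shows the average of PPV and NPV there; the truth is 0.50.

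| Search | 32 v 32 | 60 v 60 |
|---|---|---|
| one marker | 0.62–0.66 | 0.61–0.65 |
| best of four markers | 0.66–0.72 | 0.65–0.70 |
| four markers and six ratios | 0.68–0.74 | 0.67–0.73 |

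The range within a cell comes mostly from the minimum group size. Almost doubling the number of cases barely reduces the bias.

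**4. If a p-value were attached.** The protocol sets no criterion, so these rates are conditional on one. They are for 32 v 32 at one time point, as the share of null trials in which some cut-off passes Fisher's test.

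| Search | p < 0.05 | p < 0.01 |
|---|---|---|
| one marker | about 18–27% | about 5% |
| four markers | roughly 50–70% | about 15–20% |
| four markers and six ratios | roughly 75–90% | about 34–36% |

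The p < 0.01 column uses a wider set of assumed correlations (0 to 0.8) and a looser limit on group size.

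A single pre-set cut-off gives 3% at p < 0.05. Judging the smallest p against the null distribution of the whole search brings the rate back to about 5%. The nominal p required then falls to about 0.002–0.004 for four markers and about 0.001 for ten candidates.

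**The case against.** Four objections carry weight.

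- **The search is not fully specified.** Section 1.3 is background and speaks of cut-offs for the different markers, which can be read as one per marker. Ratios appear only in section 1.5, and no section describes a search over months. A reader might infer one joint search over every marker, ratio and monthly sample, in which a nominal hit is almost certain. The documents do not say that. This is why the one-marker figures stand beside the wider ones; even they are well above 0.50.
- **No success rule exists.** A reader might infer that most trials would declare a predictive marker even if none predicts, or that the endpoint is met almost whatever the data show. Both need a pass mark that the protocol does not contain, and at p < 0.01 or with a single marker the hit rate is well below half. Nor is it fair to say that a PPV of 100% can always be found: that needs groups as small as one patient and ignores NPV, while section 1.3 asks for both.
- **The data set is partly inferred.** Section 1.3 does not tie the cut-offs to the 32 and 32, and the bi-annual samples cover all patients. However, the endpoint concerns monthly measurements, and section 1.15 confines those to the cases and controls.
- **The aim is partly exploratory, and detail may sit in an analysis plan.** Prospective testing in new patients is stronger validation than any resampling of 64, and a noise cut-off should fail there. An analysis plan not shown may also add internal validation. This limits the harm to the planning of later trials, but the rule as written still yields inflated values.

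A smaller objection is that section 1.3 expects raised resorption, which could fix the direction for CTX-I and TRAP5b and narrow the search. It describes formation as biphasic, so this does not help PINP or bALP.

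**Conclusion.** The concern holds in a limited form. The protocol states a selection rule that maximises apparent performance, and the monthly data it would draw on are about 32 cases and 32 controls. If the values are reported from the same patients, a marker without any predictive content would show a PPV and NPV of about 0.62–0.66 on its own, 0.66–0.72 as the best of four, and 0.68–0.74 with ratios added, against a true 0.50. The size depends on the assumed correlations and minimum group size; the direction of the bias does not.

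No false-positive rate follows from the protocol, because it sets no criterion. The consequence is over-optimistic input to later trials, not a false confirmatory claim in this one. The reference value of 0.50 belongs to the 1:1 sample. Converting to the PBD risk in all patients is a separate matter that optimism correction does not address.

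**What to change.** Amend sections 1.3 and 1.13 before the marker data are analysed, to state that:

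1. whatever cut-off search is performed (markers, ratios, time points) will be repeated in full within bootstrap resamples or cross-validation, keeping matched pairs together;
2. optimism-corrected performance with confidence intervals will be reported in place of the apparent PPV and NPV;
3. the chosen cut-offs will be labelled exploratory and unvalidated;
4. any p-value attached to a selected cut-off will be adjusted for the whole search, for example by a max-statistic permutation test.

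A significance gate is not needed for an aim of this kind. The cost is some wording and computing, with no new patients or samples. The downside is that the reported predictive values will be lower.

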**1.4 Study Rational.**

Bone disease in MM is a common disorder leading to pain, possible fractures, hypercalcaemia and a severely reduced quality of life. Treatment with zoledronic acid does not only reduce pain and the risk of SRE but also increase overall survival. Prolonged use however, increases the risk of BON, especially in patients with reduced dental health who undertakes invasive dental procedures. No data are currently available concerning the optimal duration of zoledronic acid treatment, but two years is the most common recommendation since the original studies had a follow-up of approximately 24 months. There are data emerging that indicate that cancellation of treatment results in an increased risk of PBD.

Another completely different alternative when evaluating bone disease in MM is to use biochemical markers. This method is completely without radiation exposure, and it may in the future decide when zoledronic acid should be given and when it should be withheld, thereby reducing the risk of BON without increasing the risk of PBD.

The golden standard when evaluating bone disease in MM is still conventional radiography. Never the less, conventional radiography is a cumbersome and time-consuming investigation for the patient who usually suffers from bone pain. Furthermore, lesions, especially in the axial skeleton, can be difficult to visualise and it has been demonstrated that CT is a more sensitive modality. It is now possible to conduct low-dose CT reducing the radiation exposure to an acceptable level; indicating that it should be the modality of choice. Prospective studies however are still lacking before the precise role of low-dose CT in MM can be defined.

The purpose of this study is threefold. To determine the optimal duration of treatment with zoledronic acid. To investigate if the future role of serum bone markers in MM could be to tailor treatment to the individual patient. Finally, to evaluate if low-dose CT should replace conventional radiography as the golden standard when evaluating bone disease in MM.

Amendment: After the Nordic Myeloma Study Group began working on this protocol, zoledronic acid is becoming the preferred bisphosphonate outside clinical trials in the Nordic Region. As a consequence there are now patients outside clinical trials who have received two years of zoledronic acid treatment. These patients may be included in the trial when they have received 24 infusion with zoledronic acid. They will be randomised at the time of inclusion.

